# Dual tracer navigation for lymph node dissection in laparoscopic radical gastrectomy (DANCE trial): a protocol for a prospective, randomized clinical trial

**DOI:** 10.1186/s13063-023-07676-4

**Published:** 2023-10-02

**Keywords:** Lymph node, Indocyanine green, Carbon nanoparticles, Gastric cancer

## Abstract

**Background:**

Lymph node (LN) metastasis is the most common metastasis route in gastric cancer. Extensive dissection of LNs can significantly improve the prognosis of patients with gastric cancer. Recently, multiple clinical studies have demonstrated that either indocyanine green (ICG) or carbon nanoparticles (CNs) can assist to promote the dissection of LNs during laparoscopic radical gastrectomy. Considering the pros and cons of the two tracers, this study proposed a novel method of dual tracer (ICG combined with CNs) for lymphatic tracing in laparoscopic gastric cancer surgery.

**Methods:**

This trial is a prospective, randomized controlled trial (RCT) with an estimation of 516 participants that randomize into 4 groups (1:1:1:1), namely control group, ICG group, CNs group, and dual tracer group. The primary outcome is the number of dissected LNs. The secondary outcomes include positive rate, false positive rate, negative rate, false negative rate, number of metastatic LNs, relationship between LN metastasis and tracer stained, operation duration, blood loss, incision length, morbidity and mortality rate, 3-year DFS (disease free survival), PFS (progression-free survival), and OS (overall survival).

**Discussion:**

This study will investigate the efficacy and safety of a novel strategy using dual tracers for laparoscopic gastrectomy. The protocol has been approved by the Ethics Committee of Nanjing Drum Tower Hospital (2021-361-02). The trial findings will be published in peer-reviewed journals.

**Trial registration:**

Chinese Clinical Trial Registry (ChiCTR2100051309). Registered 18 September 2021, https://www.chictr.org.cn/showproj.html?proj=133764.

**Supplementary Information:**

The online version contains supplementary material available at 10.1186/s13063-023-07676-4.

## Introduction

Lymph node (LN) metastasis is the most common mode of metastasis in gastric cancer. Even in early gastric cancer, the rate of LN metastasis is about 2–20% [1]. Numerous studies have shown a close correlation between number of dissected LNs and accuracy of postoperative pathological staging and long-term prognosis [2, 3]. However, it is a great challenge for surgeons to identify LNs from hypertrophic adipose tissue or complex lymphoid tissue without increasing the risk of surgery and postoperative complications. Therefore, improving intraoperative visualization of LNs becomes an urgent clinical issue [4].

In recent years, navigation technique using tracers such as indocyanine green (ICG) and carbon nanoparticles (CNs) to visualize LNs has been proved to be effective for sentinel LN tracing and dissection in breast cancer, lung cancer, and other tumors [5–10]. Also, it has been confirmed that either ICG or CNs can assist surgeons to dissect LNs in laparoscopic gastrectomy. Nevertheless, there are still limitations in the application of two tracers.

ICG administration includes multi-point subserosal injection and peritumor submucosal injection [9, 11–13]. Subserosal injection of ICG can help to obtain better LN navigation, but it also usually leads to the leakage of fluorescence and spilled the surgical field [13]. Submucosal administration of ICG helps tumor localization but restrains LN visualization compared to subserosal administration.

CNs is mainly administrated by peritumoral submucosal injection under preoperative gastroscopy. CNs can induce satisfactory tumor localization due to its intuitive black staining effect and rarely brings the contamination of surgical fields. However, submucosal injection of CNs is inferior in lymphangiography because of its limited retention capacity in lymphatic vessels. In addition, the accumulation of CNs in distant LNs is much less than that in peritumoral LNs [14, 15]. Collectively, single tracer (either ICG or CNs) strategy demonstrates unfavorable technical bottlenecks. We notice that the disadvantages of ICG tracer technology can be complemented by the advantages of CNs tracer technology, and vice versa. Consequently, it is promising to implement dual tracers into laparoscopic gastrectomy for a synergistic effect in LN visualization.

## Methods

### Study design

This is a prospective, unblinded, superiority testing, randomized controlled trial. A parallel group cluster randomized controlled trial with four arms will be conducted. Figure 1 demonstrates the flow chart of current study. Figure 2 contents the schedule of enrolment, interventions, and assessments. Participants were randomized into 4 groups at a 1:1:1:1 ratio: (1) control group: participants will undergo conventional laparoscopic radical gastrectomy without any tracer; (2) ICG group: participants will undergo laparoscopic radical gastrectomy with subserosal ICG navigation; (3) CNs group: participants will undergo laparoscopic radical gastrectomy with submucosal CNs navigation; (4) dual tracer group: participants will undergo laparoscopic radical gastrectomy with both tracers, i.e., subserosal ICG and submucosal CNs. Primary and secondary outcomes will be assessed after the gastrectomy. The study protocol is reported in accordance with the guidelines outlined in the SPIRIT Checklist for Trials (Additional file 1) [16].

**Fig. 1 Fig1:**
[figure not shown]
Flow chart of this study

**Fig. 2 Fig2:**
[figure not shown]
Content for the schedule of enrolment, interventions, and assessments

### Study setting

This study is a single-center trial that will be conducted in the Division of Gastric Surgery, Department of General Surgery, Nanjing Drum Tower Hospital, the Affiliated Hospital of Nanjing University Medical School. This hospital is a large comprehensive tertiary healthcare institute that attracts patients from Jiangsu, Anhui, and other provinces in China.

### Sample size

This study is a superiority testing trial (one-tailed trial) of which the primary outcome is the number of retrieved LNs and study subjects will be divided into 4 groups. Combined with our previous findings and literature reports, the standard deviation σ of the total number of LNs in control group was 8.6 [9, 13, 17]. The *α* (test level) is set as 0.05 and power (1-β) is 0.8. A difference of more than 3 in the total number of detected LNs will be considered as significant, i.e., the effect value *d* = 3/*σ* = 0.35. Thus, at least 103 (102.3) participants are required in each group. Considering an expected dropout rate of 20%, 129 (128.75) participants are finally required in each group, leading to a total of 516 participants.

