### Data analysis

Database will be established using Epidata 3.0, and statistical analysis will be performed using SPSS 18.0. This trial uses differential testing; a *p*-value less than 0.05 will be considered statistically significant, and the confidence intervals for the parameters will be estimated as 95%.

In this trial, validity analysis based on MITT (modified intention to treat) analysis will be conducted. The primary and secondary outcomes will be analyzed with both MITT and PP (per protocol) analysis. Conclusion of MITT analysis will be the primary analytical method, and if the conclusions of PP analysis and MITT analysis are consistent, the credibility of the conclusions can be improved. SP (safety population) analysis will be used to analyze laboratory evaluations, adverse events, and adverse reaction data. SP will be defined as the denominator for the incidence of adverse reactions.

Descriptive statistics will be used to systematically describe primary and secondary outcomes. Means, standard deviations, and confidence intervals will be presented based on data from the control group and intervention groups. Frequency distributions, percentages, medians, and mean rank order will be presented based on quantitative data and rank data. Positive rates, positive number, and total number of retrieved LNs will be presented based on qualitative data. The number of events, number of missingness, median survival time, and survival rate will be presented based on survival data. Efficacy analysis will be performed on data following descriptive statistics. This study utilizes Pearson chi-square test for qualitative data, *t* test for quantitative data, Wilcoxon rank sum test for ranked data, Log-rank test for univariate analysis and Cox regression model for multivariate analysis of survival data, and two-tailed test for safety indicators and incidence of adverse reactions.

Abnormal values will be judged when the observed value is greater than P75 or less than P25, and 3 times more than the interquartile range defined as P75 subtracts P25. Sensitivity analysis will be performed on the abnormal data, and the data will be retained if results are not contradictory. If there is a contradiction, specific analysis will be conducted.

Subgroup analysis will be performed to identify risk factors for the prognosis according to the specific circumstances of the data.

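### The sample size rests on a one-tailed 5% test, but the analysis section does not carry that rule to the primary outcome and pairs p<0.05 with 95% confidence intervals

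*Protocol article*

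**What the plan says.** All references are to the protocol article.

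**Sample size.** The section declares the design: "This study is a superiority testing trial (one-tailed trial) of which the primary outcome is the number of retrieved LNs". It sets the error rates ("test level) is set as 0.05 and power (1-β) is 0.8") and the spread ("the standard deviation σ of the total number of LNs in control group was 8.6"). The target is given as "A difference of more than 3 in the total number of detected LNs will be considered as significant", which is converted to an effect size of 3/σ = 0.35. The result is "at least 103 (102.3) participants are required in each group", and then "Considering an expected dropout rate of 20%, 129 (128.75) participants are finally required in each group", or 516 in total.

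**Data analysis.** The trial is said to use differential testing. The threshold and the interval come in one sentence: "value less than 0.05 will be considered statistically significant, and the confidence intervals for the parameters will be estimated as 95" per cent. No sidedness is attached to either. The list of methods assigns a t test to quantitative data, again without sidedness, and ends with a "two-tailed test for safety indicators and incidence of adverse reactions". That is the only place in the section where the number of tails is mentioned.

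**The concern.** A one-tailed test at 5% corresponds to a two-sided 90% interval, or to a one-sided 95% bound. A conventional two-sided 95% interval corresponds to a two-sided test at 5%. The protocol sizes the trial on the first and, on the ordinary reading, reports the second.

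Two readings of the primary analysis are open, and each has its own consequence:

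- **One-tailed at 5%.** The trial can declare superiority while the published 95% interval for the difference in node count includes zero.
- **Two-sided at 5%.** The 103 evaluable participants per group do not give the stated 80% power.

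In an unblinded trial it matters that the text fixes which reading applies before results are seen, because for a band of results the primary conclusion depends on it.

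**Working it through.** **Inputs** (Sample size section): difference 3 nodes; SD 8.6; alpha 0.05; power 0.80; 103 evaluable and 129 randomised per group; dropout 20%. Effect size d = 3/8.6 = 0.349. The check is for one comparison between two groups by t test. Multiplicity over four groups is a separate matter and is left out.

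**1. Reproduce the plan's figure.** Power of a t test with n per group is the probability that a noncentral t variable, with 2n − 2 degrees of freedom and noncentrality d·√(n/2), exceeds the critical value. Solving for 80% power:

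| Test | n per group (unrounded) | Rounded up | After 20% dropout | Four groups |
|---|---|---|---|---|
| One-sided 0.05 | 102.30 | 103 | 103/0.8 = 128.75, so 129 | 516 |
| Two-sided 0.05 | 129.97 | 130 | 130/0.8 = 162.5, so 163 | 652 |

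The one-sided row matches the printed 102.3, 103, 128.75, 129 and 516. The two-sided row does not. The sizing is therefore one-sided at 5% and its arithmetic is right.

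**2. If the primary test is one-tailed at 5%.** With 103 per group:

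- Standard error of the difference = 8.6 × √(2/103) = 1.198.
- Smallest significant difference, one-tailed: t(0.95; 204) × SE = 1.652 × 1.198 = 1.98 nodes.
- Smallest difference whose two-sided 95% interval excludes zero: t(0.975; 204) × SE = 1.972 × 1.198 = 2.36 nodes.

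An observed advantage between 1.98 and 2.36 nodes is superior by the test but has a 95% interval that includes zero. The chance of landing in that band is:

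- if the true difference is 3 nodes: 80.2% − 70.3% = about 10% per comparison;
- if there is no difference: 5% − 2.5% = 2.5% per comparison.

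**3. If the primary test is two-sided at 0.05.** Power for a true difference of 3 nodes, SD 8.6:

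| Analysed per group | One-sided 0.05 | Two-sided 0.05 |
|---|---|---|
| 103 (20% lost) | 80.2% | 70.3% |
| 116 (10% lost; 129 × 0.9 = 116.1) | 84.2% | 75.4% |
| 129 (none lost) | 87.5% | 79.7% |
| 130 | 87.7% | 80.0% |

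The normal approximation gives 70.7% instead of 70.3% at 103 per group, so the shortfall of about 10 points does not depend on the method.

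**The case against.** The strongest defence is that the two sections can be read together. The design is openly declared one-tailed, and naming a two-tailed test for safety alone suggests that efficacy is tested one-tailed. On that reading the sections agree on sidedness and the stated 80% is true of the declared test. The 95% interval is then a general reporting convention covering all outcomes. Nothing makes it the criterion for superiority, and a one-sided 95% bound would match the test exactly.

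Much of this stands. A reader might infer that the sample size is miscalculated, or that the trial simply has 70% power. The document does not support either: 103, 129 and 516 follow from the declared inputs, and 70% arises only if the primary test is two-sided, which no section prescribes. A reader might also infer that the protocol doubles its own error rate. It does not, because the only level it declares is 0.05, and 2.5% comes from the convention behind a two-sided 95% interval. Nor can the power loss and the interval crossing zero be charged together, since they belong to different readings.

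What the defence leaves open is that the one-tailed rule for efficacy has to be inferred from a remark about safety, in a section that describes differential testing at p<0.05 and gives no sidedness for the interval. Even on the defence's reading, the test and a conventional 95% interval can disagree.

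**Conclusion.** The point holds as an inconsistency between the Sample size and Data analysis sections, not as an arithmetic error. As written, the protocol leads to one of two outcomes. Either results of about 1.98 to 2.36 nodes are called superior with a two-sided 95% interval that includes zero, or the test is two-sided and power is about 70% where 80% is stated.

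These figures assume 103 analysed per group, an SD of 8.6 in both groups, a true difference of 3 nodes for the power, and that the 95% interval is the usual two-sided one. If the interval is meant as a one-sided 95% bound, the conflict on the first reading disappears, but the protocol would have to say so.

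A reader might also infer that the 129 randomised per group already supply 80% two-sided power, so that nothing is lost. The figure is 79.7%, and only if the whole dropout allowance goes unused. The Withdrawal criteria (among them M1 or T4b findings, incomplete D2 or R0, and protocol violation) and the data management rule that withdraws participants with missing data work against that.

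**What to change.** State one sidedness and one level for the primary test, in the same words, in both the Sample size and Data analysis sections, and name the matching interval.

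- **Preferred:** two-sided 0.05 (equivalently one-sided 0.025) with the 95% interval. Restate power as about 70% at 103 evaluable per group, about 75% at 116, and just under 80% (79.7%) only if all 129 are analysed. To rely on the last figure, the protocol must also say that the withdrawal and missing-data rules do not remove operated patients from the primary analysis. If the 20% loss is kept and 80% power is wanted, the requirement is 130 evaluable and 163 randomised per group, 652 in total against 516.
- **Alternative:** keep one-sided 0.05, say so explicitly for the primary outcome in the Data analysis section, and report a 90% two-sided or one-sided 95% interval for it. The sample size and the stated 80% then stand.

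Under either option the essential change is wording. The cost of the preferred option is a less favourable stated power at 103 per group, or more patients if 80% is to be kept with the planned dropout.

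### The sample size covers one unnamed pairwise contrast in a four-arm trial, so the stated 5% error and 80% power hold for one pair of arms and not for the trial's conclusion

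*Protocol article*

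**What the plan says.** All references are to the protocol article.

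- **Sample size, design:** the section opens with "This study is a superiority testing trial (one-tailed trial" and adds that the "primary outcome is the number of retrieved LNs and study subjects will be divided into 4 groups".
- **Sample size, inputs:** the "test level) is set as 0.05 and power (1-β) is 0.8". The standard deviation is given for one arm only: "the total number of LNs in control group was 8.6". The target is worded without naming two arms: "A difference of more than 3 in the total number of detected LNs will be considered as significant".
- **Sample size, result:** "Thus, at least 103 (102.3) participants are required in each group". With 20% dropout this becomes 129 per group, and four groups make 516.
- **Data analysis:** quantitative data are analysed by t test, and a p-"value less than 0.05 will be considered statistically significant, and the confidence intervals for the parameters will be estimated as 95" per cent. The section gives no overall four-group test, order of testing or division of alpha.
- **Introduction and Discussion:** both argue that two tracers overcome the limits of either tracer alone. The Discussion sets out expected advantages over ICG alone and over CNs alone. Neither section, nor Methods, turns this into a formal hypothesis about the node count.

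**The concern.** Four arms give six possible pairwise contrasts on the primary outcome. The plan sizes one of them without saying which, and its significance rule applies equally to all six. A reader of the results could not tell whether a claim that dual tracer is superior rests on a contrast chosen beforehand or on whichever one crossed 0.05.

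The contrasts also mean different things. Beating no tracer is a weaker result than beating ICG alone or CNs alone, and the rationale for a dual-tracer arm rests on the latter two. Error rate and power both depend on which contrasts must succeed, so until that is fixed neither stated figure belongs to the trial's conclusion.

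**Working it through.** **Inputs (Sample size section):** difference 3, SD 8.6, one-sided alpha 0.05, power 0.80, 103 evaluable per arm, four equal arms.

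**1. The plan's own figure.** With d = 3/8.6 = 0.349, a two-sample one-sided t test (noncentral t) needs 102.30 per group, which matches the stated 102.3. The two-sided version needs 130, which does not match. Then 103/0.8 = 128.75, rounded up to 129, and 4 × 129 = 516. The arithmetic is correct for one one-sided pairwise test.

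**2. Power for one pair at 103 per arm.**
- Standard error of a difference = 8.6 × √(2/103) = 1.198.
- Expected z = 3/1.198 = 2.503.
- Power = Φ(2.503 − 1.645) = Φ(0.859) = 80.5%.

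**3. Error if any significant contrast counts.** Four equal arms with no true differences, each test at 0.05. Contrasts that share the dual arm have correlation 0.5.

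| Contrasts tested | P(at least one false positive) |
|---|---|
| Dual vs ICG, dual vs CNs (one-sided) | 8.8% |
| Dual vs each of the other three arms (one-sided) | 11.8% |
| All six pairs (two-sided) | 20.3% |

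The first two come from simulation of four arm means and agree with the multivariate normal integral. The third agrees with the studentized range distribution for four groups.

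**4. Error if dual must beat both single tracers.** Both tests have to reject. If dual is no better than at least one single tracer, a false claim requires the test against that tracer to reject wrongly, which happens at most 5% of the time. No alpha adjustment is needed.

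**5. Power if dual must beat both.** Assume a true gain of 3 nodes over each single tracer and SD 8.6 in all arms. Power is the bivariate normal probability, with correlation 0.5, that both standard normals fall below 2.503 − c.
- One-sided 0.05 (c = 1.645): 69.4%.
- One-sided 0.025 (c = 1.960): 56.5%.

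**6. Power to pass dual vs control, then dual vs ICG, then dual vs CNs, each at full alpha.** This is the same calculation with three contrasts. A 6-node gain over control gives an expected z of 6/1.198 = 5.007 for the first step, so that step is almost always passed.

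| True gain of dual | One-sided 0.05 | One-sided 0.025 |
|---|---|---|
| 3 over every other arm | 61.9% | 47.8% |
| 6 over control, 3 over each single tracer | 69.4% | 56.5% |

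**7. Size for 80% power to beat both single tracers** (one-sided 0.05, assumptions of step 5): 131 evaluable per arm; 131/0.8 = 163.75, so 164; 4 × 164 = 656 in total.

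**The case against.** **The two faults do not occur together.** A reader might infer that the trial has both an inflated error rate and a shortfall in power. That is not supported. If any win counts, the error is inflated and the 69% is beside the point. If dual must beat both single tracers, the error is controlled and only power suffers. The plan does not say which rule applies, so each figure is conditional on its rule.

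**A flat false-positive rate of 12 to 20% is too strong.** That range needs a family of three to six contrasts, which the protocol does not define, and it mixes one-sided with two-sided tests. For the two single-tracer contrasts the rate is about 9%. Every figure assumes that no arms differ. This objection stands in full.

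**Beating both tracers by 3 nodes is not a stated hypothesis.** It is inferred from the Introduction and Discussion. The advantages listed over ICG alone are fewer false negatives, better tumour localization and less field contamination, not a higher node count. The SD is given for control only. This also stands: the 69% is a scenario, not the trial's power.

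**An unseen analysis plan may contain a multiplicity procedure.** It may, and its absence from an article is not in itself a fault. But the sample size is fixed in this document for one pair, and a procedure elsewhere would not change that. An alpha split would lower power: Bonferroni over three contrasts leaves 64.6% per contrast at 103 per arm (one-sided).

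**Conclusion.** The point holds in a conditional form. The stated 103 per arm is arithmetically right for a single one-sided contrast between two unnamed arms, and the significance rule does not single out any contrast. The 5% and 80% therefore do not carry over to a conclusion drawn from four arms.

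The size depends on the decision rule, which the sponsor has to supply. Under an any-contrast rule the false-positive rate is about 9%, 12% or 20% for the three families shown, given no true differences. Under a rule that dual must beat both single tracers, the error is at most 5% and power is about 69% at one-sided 0.05, given a gain of 3 nodes over each and a common SD of 8.6. The documents do not support the claim that the sample size was miscalculated, or that the trial as written has one particular inflated error rate.

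**What to change.** Before outcome data are compared between arms:

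1. **Name the primary contrasts and a procedure that holds the overall error at 0.05.** One option is a fixed sequence: dual vs control, then dual vs ICG, then dual vs CNs, each at full alpha, stopping at the first non-significant result. Other valid procedures exist. The order is the sponsor's choice and should be justified.
2. **Report the remaining pairs** (ICG vs control, CNs vs control, ICG vs CNs) as estimates with confidence intervals, without claims of significance.
3. **Amend the Sample size section** to say that 80% applies to one contrast, and state the power to pass the whole sequence with its assumptions. At one-sided 0.05 this is about 62% if dual exceeds every arm by 3 nodes, and about 69% if it exceeds control by about 6 and each single tracer by 3. At one-sided 0.025 the figures are about 48% and 56%.

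The cost is wording in the protocol and analysis plan, with no additional patients. The downsides are that later contrasts cannot be claimed once an earlier one fails, and that the stated power becomes less favourable. This makes the power statement accurate but does not raise the power. If the sponsor wants 80% for beating both single tracers, that is a separate decision, at 656 patients in place of 516.
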